### Explanatory variables: IC composite index (ICI)

An IC composite score or index (IC index or ICI) will first be created, as suggested by Gutiérrez-Robledo et al. (2019). This score aims to express a summary measure of impairments for an older adult. Initially, each continuous or ordinal subdomain measure will be dichotomized based on acceptable cut-off points to create a binary variable of 0 or 1 (see Table 3 for cutoff points across all subdomain measures). Within a domain, the values of these recoded subdomain measures will be summed up to create a “subdomain score.” The subdomain scores will range from 0 to 2 for the four subdomains with only two measures and from 0 to 6 for the subdomain with six measures (i.e., vitality). Then, each domain of the five IC components will be subdivided into three categories based on the sum of the scores of its subdomains, with the following numerical score: no impairment = 0, mild impairment = 1, and severe impairment = 2. For example, the four domains with only two subdomain measures (e.g., cognitive with subdomain measures memory and cognitive) will be coded 0 if their subdomain score (sum of their subdomain measure) is 0, 1 if the subdomain score value is 1, and 2 if the subdomain score value is 2. The domain with six subdomain measures, vitality (subdomains comorbidity, medication, biomarkers, pain, strength, and nutrition), will be coded 0 if its subdomain score is 0, 1 if the subdomain score is 2–4, and 2 if the subdomain score is 5–6. Scores for each of the five domains will be summed up to produce a composite IC index ranging from 0 (best possible ICI) to 14 (worst possible ICI).

Subsequently, this baseline ICI will be classified in four ways. First, using the terciles of ICI (TIC), ICI values less than or equal to the first tercile (Q1) will be classified as low TIC; ICI values between Q1 and the third tercile (Q3), including Q3, will be classified as medium TIC; and ICI values above Q3 will be classified as high TIC. This analysis model is explicitly shown in Figure 1.

Second, the change in the ICI value during the follow-up time in the cohort will be measured and referred to as “ICI delta” (∆IC). The ∆IC is calculated as the difference between the ICI measured in the last follow-up wave minus the ICI measure at the baseline (variable with values between 0 and 10). Third, we will consider the presence of a decline in IC (DIC) if one or more declines in an IC domain are found from the baseline measure. As an example of IC domain decline in the cognitive dimension, a Montreal Cognitive Assessment (MoCA) score of 22 at follow-up versus 27.0 at baseline is considered a decline and probable “dementia” (Nasreddine et al., 2005). The opposite will be classified as no decline.

Finally, a weighted measure of IC (WIC) will be derived from the multivariate regression result of the association between IC subdomains and IADL loss, which will be adjusted for individual sociodemographic factors (see the Analysis section below for detailed description of WIC).

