In contrast, we should also be able to model Y as ∆IC (ordinal variable with values from 0 to 10) as a function of a main vector X (IADL, falls, or death) and a collection of parameters V and W similar to the previous model, but using a multivariate ordinal regression model with a latent variable specification, where composite probability methods are applied to estimate model parameters (Hirk et al., 2019).

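### The ICI scoring rule gives no code to a vitality score of 1, and the stated ranges of ICI (0–14) and ∆IC (0–10) and the sign of ∆IC do not follow from it

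*Protocol article*

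**What the plan says.** All of this is in the protocol article.

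- **Items.** Under Explanatory variables: IC composite index (ICI), each measure is "dichotomized based on acceptable cut-off points to create a binary variable of 0 or 1". Table 3 lists 14 of them: six for vitality and two for each of the other four domains. The sums within domains therefore run "from 0 to 2 for the four subdomains with only two measures and from 0 to 6 for the subdomain with six measures".
- **Domain codes.** Each domain is then put into three categories: "no impairment = 0, mild impairment = 1, and severe impairment = 2". For a two-item domain the code is 0 if the sum "is 0, 1 if the subdomain score value is 1, and 2 if the subdomain score value is 2". For vitality it is 0 if the sum is 0, "1 if the subdomain score is 2–4, and 2 if the subdomain score is 5–6".
- **Index.** The five domain scores are added to give a "composite IC index ranging from 0 (best possible ICI) to 14 (worst possible ICI").
- **Change.** ∆IC is the ICI at the last wave minus the ICI at baseline, described as a "variable with values between 0 and 10". The section on statistical models for IC as a predictor repeats this for the ordinal regression: "ordinal variable with values from 0 to 10".
- **Hypothesis.** Research question 1 expresses the expected fall in capacity as ∆IC below zero and tests ∆IC = 0.

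**The concern.** Building the ICI is the second objective and its trajectory is the fifth. Its terciles (TIC) are the exposure in the first Cox model. ∆IC carries research question 1 and is the outcome of the ordinal model. A rule that fails for one value of one domain therefore reaches all of these analyses. The weighted score (WIC) is built directly from the dichotomised measures and is not affected.

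A vitality score of 1 is not an odd case: a single positive item, such as a body mass index above 25, produces it. If the code is chosen only once data are in hand, the analyst has a free choice that moves people between terciles. The wrong ranges and the reversed sign matter in a different way. They tell a programmer or reader to expect values that the rule cannot give, and they leave unclear which sign of ∆IC would support the hypothesis.

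**Working it through.** **Inputs.** All come from the ICI section and Table 3: 14 binary items (6 vitality, 2 in each of four other domains); domain codes 0, 1 or 2; ICI = sum of five domain codes; ∆IC = follow-up ICI − baseline ICI.

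**1. The vitality map as written.**

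| Vitality score | 0 | 1 | 2 | 3 | 4 | 5 | 6 |
|---|---|---|---|---|---|---|---|
| Code | 0 | none | 1 | 1 | 1 | 2 | 2 |

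Of the 2^6 = 64 vitality patterns, 6 have a score of 1. Across all 2^14 = 16,384 patterns of the 14 items, 6 × 2^8 = 1,536 have no defined ICI.

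**2. How many people this could be.** The article gives no item prevalences. Assume six independent items with common prevalence q. Then P(score = 1) = 6q(1 − q)^5:

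| q | 0.1 | 0.2 | 0.3 | 0.4 | 0.5 |
|---|---|---|---|---|---|
| P(score = 1) | 35.4% | 39.3% | 30.3% | 18.7% | 9.4% |

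**3. Range of ICI.** The stated maximum of 14 is reproduced only by adding the raw items, 6 + 2 + 2 + 2 + 2 = 14, which skips the recoding into three categories. Following the rule, the maximum is 5 × 2 = 10. Enumerating all patterns gives 0 to 10 whether a vitality score of 1 is left out, coded 0 or coded 1.

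**4. Range of ∆IC.** With ICI from 0 to 10, the minimum change is 0 − 10 = −10 and the maximum is 10 − 0 = +10. The Eligibility section asks that nobody has a CDR above zero at baseline. If that is applied strictly, the cognitive domain is at most 1 at baseline, baseline ICI is at most 9, and ∆IC runs from −9 to +10. A raw sum of 14 items would give −14 to +14. No reading gives both 0–14 for the index and 0–10 for its signed change.

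**5. Sign of ∆IC.** The article's own example of decline is a MoCA of 27 at baseline and 22 at follow-up. Table 3 codes 25 or more as 0 and below 25 as 1, so the item moves from 0 to 1. With everything else unchanged, the cognitive domain moves from 0 to 1 and ∆IC = +1. Decline is therefore positive on the written scale, and research question 1 has it negative. On that scale, the interval 0–10 covers worsening and leaves out improvement.

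**The case against.** The strongest reply is that these are slips whose intent can be recovered. The category labels reserve 0 for no impairment, and a score of 1 falls short of severe, so mild is the natural inference. The 0–10 figures given for ∆IC match the maximum that the rule gives for the index, so 14 is most plausibly the item count carried over. This is fair on intent, but no sentence assigns the code, and coding a score of 1 as 0 remains a possible alternative.

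Three stronger readings are tempting and are not supported.

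- **The test of ∆IC = 0 is biased toward finding change.** That would require negative values to be truncated or dropped. No passage says so, ∆IC is defined as a signed difference, and research question 1 itself uses negative values. The bias is conditional on someone enforcing the 0–10 range.
- **Two rival indices exist, with vitality at 6/14 (43%) or 2/10 (20%) of the maximum score.** The article describes only one rule, the sum of recoded domains. The raw 14-item sum is an inference from the number 14.
- **A fixed share of the cohort will lack an ICI.** The percentages rest on equal, independent prevalences. Number of morbidities and number of medications are unlikely to be independent, and at q = 0.6 the same formula gives 6 × 0.6 × 0.4^5 = 3.7%.

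It may also be said that the full protocol could settle the matter. That would answer an omission, but here the article states a rule and ranges that contradict each other.

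**Conclusion.** The point holds in four parts. The vitality code for a score of 1 is missing, and this is the part that needs a decision before ICI can be computed. The ICI range should be 0–10, not 0–14. The ∆IC range of 0–10 is wrong for a signed difference. The sign of ∆IC for a loss of capacity conflicts between the ICI section and research question 1. All four follow from the written rule without assumptions.

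Only the size of the vitality gap is assumption-based: about 9% to 39% for independent items at 10% to 50% prevalence, as an illustration. The two range statements do not by themselves alter any computed value. They would lose improvements, and bias the test of ∆IC = 0, only if imposed in the analysis.

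**What to change.** 1. Code vitality by its score: 0 for a score of 0, 1 for scores 1–4, 2 for scores 5–6. This agrees with the category labels and with the two-item domains, where a score of 1 is already coded 1. The sponsor should confirm it as the intended rule. Word it by score, not by number of impaired items, because Table 3 codes the stronger handgrip as 1.
2. State that ICI is the sum of the five domain scores, with range 0–10.
3. State that ∆IC is signed, from −10 to +10 (−9 to +10 if baseline CDR must be 0), in both places where 0–10 now appears, and fit the ordinal and other models to the full range.
4. Either correct research question 1 so that decline is ∆IC > 0, or reverse the index so that higher is better. Then check the tercile labels against the chosen direction.

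The cost is a few wording corrections. The Data Availability statement says that no data have been collected, so nothing has to be re-measured or re-analysed.

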**FIGURE 1 F1:**
[figure not shown]
Proposed study design.

In a period of 6 months, we expect that a team of trained interviewers will contact all potential cohort participants. Based on information from a recent study on the association of IC with the outcome incidence rates of functional dependence, falls, and death (Prince et al., 2021), we developed sample size estimates for comparing two proportions that represent the rates of outcomes in the groups that are exposed (low IC) and unexposed (medium or high IC) (see Tables 1, 2). Calculations considered various effect sizes (relative risk) and incidence or mortality rates. In estimating the sample size needed for this cohort study, this study considered the incidence of the expected outcome in the unexposed cohort (high IC), the risk assumed in the exposed group relative to the risk of the unexposed group (RR), a specific level of confidence (1-α = 0.95; where α = type I error rate), and a specific value of the desired sample power (1-β = 0.80; where β = type II error rate) for the detection of significant differences between the two cohorts. The outcome incidence rate in the cohort was used as a proxy for the expected outcome incidence rate in the unexposed group (high IC). The summary tables (Tables 1, 2 below) provide sample sizes for extremes of the assumed incidence and mortality rate values and the respective relative risks based on the confidence intervals of these measures. A total sample size of approximately 5,500 individuals (assuming 2,750 per group) will be sufficiently robust to maintain the desired power under most diverse scenarios and varying parameters, even if the dropout rate reaches approximately equal to 15% in the two cohorts. The exception will be with very small estimates of the relative risk of death (RR ≤ 1.3).

**TABLE 1 T1:** Sample sizes for specific values of functional loss (FL), incidence, and relative risk for intrinsic capacity (IC) and FL.

	Average risk ratio	Low risk ratio	High risk ratio
Risk ratios (RR)	1.91	1.7	3.0
Incidence rate among the unexposed group	0.0495	0.04925	0.04925
Confidence level (1-α)	0.95	0.95	0.95
Power (1-β)	0.8	0.8	0.8
Study type	Cohort	Cohort	Cohort
Sample per group (n_i_)	514	816	138
Total sample (n_1_+n_2_)	1,028	1,632	276

**TABLE 2 T2:** Sample sizes for specific values of total mortality (TM) and relative risk for IC and TM.

	Average risk ratio	Low risk ratio	High risk ratio
Risk ratios (RR)	1.66	1.3	2.0

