## Research questions and hypotheses to test

This proposed research will answer three scientific questions:1. Whether IC will decrease as expected at the 3-year follow-up (ICI at end-time ≤ ICI at baseline, or ∆IC < 0), regardless of the socioecological context, individual sociodemographic, behavioral, and clinical factors, and comorbidities (Charlson et al., 1987). This research will statistically test the hypothesis that ICI will not change over time (i.e., follow up IC = baseline IC, or ∆IC = 0).2. If DIC (or TIC) at baseline will be a strong predictor of FA, such as ADL (Mlinac and Feng, 2016), IADL (Hokoishi et al., 2001), falls (Kitcharanant et al., 2020), and death, regardless of the socioecological context, individual sociodemographic, behavioral, and clinical factors, and comorbidities (Charlson et al., 1987). That is, whether the proportion of these ADL/IADL losses, falls, and deaths will be greater in the decline group (e.g., DIC present) than in the unexposed group (e.g., DIC absent). Research will statistically test the hypothesis that there is no association between IC and ADL (or IADL) (e.g., relative risk for TIC or DIC and IADL = 1).3. Whether IC and its five domains are directly associated with a measure of QoL (i.e., World Health Organization Disability Assessment Schedule 2.0 (WHODAS 2.0)) (Prüss-Ustün et al., 2017) and LTPA (i.e., the International Physical Activity Questionnaire (IPAQ)) (Craig et al., 2003), regardless of the socioecological context, individual sociodemographic, behavioral, and clinical factors, and comorbidities (Charlson et al., 1987). Research will statistically test the hypothesis that there is no association between IC and either QoL or LTPA (e.g., relative risk for TIC or DIC and LTPA = 1).

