### Generation of weighted IC score (WIC)

To build the weighted IC score (WIC), first, associations between subdomains of IC domains (sensory, mobility, vitality, cognitive, and psychological) and IADL loss will be evaluated by IADL models in a two-stage logistic regression (Meng et al., 2022). For this purpose, IC subdomains will be dichotomized, such as body mass index (BMI) (overweight–obese v. normal–underweight) and handgrip strength (normal–strong v. weak), both of which are subdomains of the vitality domain (Chen et al., 2020). The first stage of modeling requires bivariate analysis between each IC subdomain and IADLs to identify candidate subdomains to enter the multivariate logistic model (Meng et al., 2022). For this, the variable in the model whose *p-*value for the statistical test of association (chi-square) with IADL is less than or equal to α = 0.25 will enter the multivariate logistic regression model with adjustment for the sociodemographic, comorbidity, behavioral, and clinical factors. An exception will be variables selected *a priori* since they are clinically fundamental, such as BMI from the vitality domain.

In the multivariate logistic regression model, subdomains whose *p-*values are less than or equal to α = 0.05 (statistically significant) will be used to generate WIC as follows. For the regression coefficient in the multivariate model that reaches statistical significance (*p ≤* 0.05), its component will be transformed into a subdomain score by dividing the coefficient by the smallest regression coefficient in the model after rounding the absolute value of the coefficient to the nearest integer value. Regression coefficients that are not statistically significant in the adjusted model will have a value of one (1) point. A summary WIC will be obtained by adding points from all regression components. The subdomain terms will enter the multivariate regression model such that the higher the WIC score, the better the IC.

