#### Statistical models to assess whether IC is a predictor of ADLs/IADLs, falls, and death

Two Cox regression models will be evaluated to estimate the incidence rates of outcomes (i.e., functional loss measured by IADLs, falls, and death) associated with IC at baseline (e.g., TIC, DIC, and WIC) (ElHafeez et al., 2021). Cox’s first model has the indicator variable X to denote the association with each of the two groups of IC exposure at baseline (e.g., X1 = 1 for medium and high TIC and X1 = 0 for low TIC), with Y being the adverse incident at 3 years of follow-up (loss of ADLs/IADLs, falls, and death); survival times will be measured by the interval from the first assessment to the adverse incident. For subjects who do not experience an adverse incident, the follow-up time will be the last evaluation of the study.

The model also comprises a collection of covariates V with the potential to be a confounding factor in the association between Y and X (e.g., sociodemographic factors), and W would be the potentially interactive term between X and V (e.g., sex * TIC). The regression coefficient of X describes the effect of TIC on outcome Y, that is, the risk of greater or lesser loss of ADL/IADL, falls, and death for those exposed to medium or high TIC relative to those exposed to low TIC. The W terms will assess whether there is a positive interaction between TIC and one of the V confounders that have been identified to be potentially interacting. The model will extend by substituting TIC for DIC or WIC as the main exposure variable X. Alternatively, we can also model Y (e.g., IADL) as a function of X (either TIC, DIC, or WIC) and the same set of V and W using logistic regression to estimate the odds ratio of the outcomes.

We will evaluate the IC trajectory through changes in IC scores (∆IC or WIC) or the presence of IC decline (DIC) after 3 years, along with their associations with IADL outcomes, falls, and death. For example, the mean/median of ∆IC (or WIC) and the prevalence of DIC will be generated at baseline and at the end of the 3-year follow-up. We will then generate the mean/median or prevalence of IC measure by levels of ADL/IADL, falls, and death. The means/medians of IADLs and the incidence of falls and death after 3 years of follow-up will also be estimated.

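### The IC index rises with impairment, but the sample-size exposure, research question 1 and the weighted score treat higher as better, and the Cox tercile contrast is not the one the sample size assumes

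*Protocol article*

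**What the plan says.** All references are to the protocol article.

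- **Scoring of the index** (Explanatory variables: IC composite index). The purpose is given as "This score aims to express a summary measure of impairments for an older adult". Each domain is coded "no impairment = 0, mild impairment = 1, and severe impairment = 2", and the domain scores are added to a "composite IC index ranging from 0 (best possible ICI) to 14 (worst possible ICI". Higher is worse.
- **Tercile labels** (same section). "ICI values less than or equal to the first tercile (Q1) will be classified as low TIC". Values above the upper cut are high TIC.
- **Change score** (same section). ∆IC is the ICI at the last wave minus the ICI at baseline, with a stated range of 0 to 10. The Data analysis section repeats that range for the ordinal model.
- **Exposure in the sample size** (Study sample size and power calculation). The compared proportions are those in the "groups that are exposed (low IC) and unexposed (medium or high IC" groups, with planned RRs from 1.3 to 3.0.
- **Research question 1** (Research questions and hypotheses to test). "Whether IC will decrease as expected at the 3-year follow-up (ICI at end-time ≤ ICI at baseline", which the text equates with ∆IC < 0. The null to be tested is ∆IC = 0.
- **WIC** (Generation of weighted IC score). It is built so that "the higher the WIC score, the better the IC".
- **Cox model** (Statistical models to assess whether IC is a predictor of ADLs/IADLs, falls, and death). The coding is "X1 = 1 for medium and high TIC and X1 = 0 for low TIC". DIC or WIC is then put in the place of TIC as the main exposure.

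**The concern.** An index that counts impairments can be used consistently, and so can an index of capacity. The article moves between the two without reversing the score anywhere in the text shown.

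Three things are at stake. The group called low in the analysis is not the group called low in the sample-size calculation, so the estimated ratio is not the planned one. A loss of capacity moves ∆IC in the direction opposite to that written in research question 1, so a literal reading would count an improvement as the expected decline. TIC and WIC would also give opposite signs for the same relationship in the same model slot, and the model section gives no warning of this.

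**Working it through.** **1. The plan's own figures.** For two proportions, 1:1, two-sided α = 0.05 and power 0.80, n per group = (1.960 + 0.842)² × [p₁(1−p₁) + p₀(1−p₀)] / (p₁−p₀)², where p₁ = RR × p₀ and (1.960 + 0.842)² = 7.849.

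- Functional loss (Table 1, average RR): p₀ = 0.0495 and RR = 1.91 give p₁ = 0.0945 and n = 513.1, rounded up to 514. Stated: 514.
- Death (Table 2, average RR): p₀ = 0.04826 and RR = 1.66 give p₁ = 0.0801 and n = 925.5, rounded up to 926. Stated: 926.

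Both are reproduced. They assume RR > 1 for low IC, meaning poor capacity.

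**2. Direction in each place.**

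| Place | What a high value or label means |
|---|---|
| ICI scoring | more impairment |
| TIC labels | high = more impairment; low = best third |
| ∆IC (last minus baseline) | positive = loss of capacity |
| Sample size | low IC = at risk, so high = better |
| Research question 1 | decline = ∆IC < 0, so high = better |
| WIC | high = better |
| Cox coding of TIC | X1 = 1 for medium/high TIC, the more impaired groups under the ICI scoring |

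The sample size, research question 1 and WIC disagree with the ICI scoring. The Cox coding does not.

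**3. The contrast moves as well as the sign.** The sample size compares poor capacity with the rest. Under the TIC labels, low versus medium/high compares the best third with the rest. The article gives no risks by third, so two patterns are assumed, each with risk p₀ in the best third and RR × p₀ in the worst.

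*Flat: the middle third also has risk p₀.*
- Worst third versus the rest: RR.
- Low TIC versus medium/high as labelled: p₀ / [(p₀ + RR·p₀)/2] = 2/(1 + RR).
- Death: 1.66 becomes 2/2.66 = 0.75. Functional loss: 1.91 becomes 2/2.91 = 0.69.

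*Graded: the middle third has risk p₀√RR.*
- Worst third versus the rest: 2RR/(1 + √RR). As labelled: 2/(√RR + RR).
- Death (√1.66 = 1.288): 3.32/2.288 = 1.45 becomes 2/2.948 = 0.68.
- Functional loss (√1.91 = 1.382): 3.82/2.382 = 1.60 becomes 2/3.292 = 0.61.

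The Cox coding reports the inverse of the as-labelled ratio. For death, flat, that is 2.66/2 = 1.33. It is above 1, as expected for the more impaired groups, but it is neither 1.66 nor 1/1.66.

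**4. Power.** With 5,500 × 0.85 = 4,675 participants, a 1:2 tercile split and a two-sided test of two proportions at α = 0.05:

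| Outcome, pattern | Worst third vs rest | Best third vs rest |
|---|---|---|
| Death, flat | 0.99 | 0.59 |
| Death, graded | 0.90 | 0.87 |
| Functional loss, flat | >0.99 | 0.85 |
| Functional loss, graded | 0.99 | 0.99 |

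A marked loss of power appears only in the flat pattern, so the point does not rest on it.

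**5. Change score.** If the ICI rises from 3 to 4, capacity has been lost and ∆IC = 4 − 3 = +1. Research question 1 calls for ∆IC < 0. The stated range of 0 to 10 excludes every negative value, so it cannot accommodate that hypothesis or any improvement. Five domains scored 0 to 2 give a maximum of 5 × 2 = 10, not 14; the figure 14 is the number of items (6 + 4 × 2).

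**6. Items.** Table 3 codes stronger handgrip as 1, while elsewhere the table uses 1 for the impaired state. Reversing the total would not remove this mixture.

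**The case against.** A reader might infer that every main contrast comes out reversed and that the cohort's central questions would be answered backwards. The document does not support that.

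- **Cox model.** Under the ICI scoring, medium/high TIC is the more impaired group. Coding it as 1 gives a hazard ratio above 1 in the natural direction. This stands; the conflict is with the sample-size section's exposure and with the choice of which third is set against the rest.
- **Research question 1.** The formal null is ∆IC = 0, and a two-sided test does not depend on the sign. This stands; the fault is in the stated direction of the expected change.
- **DIC.** It is defined by decline in a domain, and its MoCA example (27 at baseline, 22 at follow-up) runs the right way. DIC analyses are unaffected by the tercile labels.
- **Simple inversion.** A reader might take 1/1.66 = 0.60 as the size for death. That assumes the same two groups change places. They do not, because the cut moves from the worst third to the best.
- **WIC.** Its direction is stated openly, and opposite-signed coefficients can be interpreted. This stands in part: the model section should say so when WIC takes the place of TIC.
- **Figure 1.** It is cited as showing the tercile model but is not available here, so it may clarify the labels. It could not reconcile research question 1 with the written definition of ∆IC.

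**Conclusion.** The inconsistency is real and should be corrected before data collection. As scored, low TIC is the best-capacity third, while the sample size needs low IC to be the at-risk group. Research question 1 gives the wrong sign for decline under the article's own definition of ∆IC, and WIC enters the same model slot as TIC with the opposite direction.

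The TIC contrast therefore differs from the planned one in both its labels and its cut. For death, the planned low-versus-rest ratio of 1.66 would appear as about 0.75 (flat), or 1.45 as about 0.68 (graded). For functional loss, 1.91 would appear as about 0.69, or 1.60 as about 0.61. These sizes rest on assumed risk patterns across thirds; the change of direction occurs in both. The stated sample sizes do not change, because they already assume poor capacity as the exposure.

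**What to change.** Choose one direction for all IC measures and carry it through. One workable set:

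- Define ICI = 10 minus the sum of the five 0–2 domain scores, so that higher is better, and correct the stated maximum of 14.
- Use two tercile cuts, the 33.3rd and 66.7th percentiles. Three groups have only two cuts, so the reference to a third tercile should go; if Q1 and Q3 were read as quartiles, the split would be 25/50/25.
- Define low IC as the worst-capacity third, coded X = 1, against medium/high coded X = 0, and reword the interpretation of the Cox coefficient to match.
- State that ∆IC ranges from −10 to +10 and that, with the reversed index, a negative value means decline. Correct the range in both the index section and the ordinal-model paragraph.
- Recode handgrip in Table 3 so that 1 = weak.
- State the direction of WIC again where it replaces TIC.

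The sample-size section, Table 3, the index section, the research questions, the WIC section and the model sections must then be checked against each other. The cost is protocol and analysis-plan wording only; the Data Availability statement says that no data have been collected.
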